#### ***Logbook***

A 'monitoring logbook’ will be used to document screening, adherence to the intervention, unwanted symptoms, adverse events, and self-reported symptom assessment and activity levels. All components of the intervention performed will be recorded on-going including; exercise mode, frequency, intensity, duration and progression as well as subjective exercise response (BORG) and heart rate. Components performed beyond that prescribed in the intervention program, i.e. weekends or evenings, will be reported by the patient and then documented. For each individual component in the programme, adherence to the intervention will be measured by calculating the percentage of recommended exercise sessions performed by the patient (number of sessions performed /number of sessions prescribed). The *control group* will receive a modified logbook and will be asked to register activity/exercise mode, frequency and duration [59], weekly, during the study period as well as register symptom prevalence, intensity and interference (weekly) using the symptom assessment scales MDASI [56] and BFI [57].

#### ***Tracking and monitoring adverse events***

Patients will be monitored for unwanted symptoms and adverse events during each intervention session and throughout the intervention period. The following study procedures will be incorporated to ensure safety: 1) Prior to each exercise session, the patient will be monitored for blood pressure, pulse, temperature and thrombocyte and hemoglobin levels according to the study’s screening criteria; 2) During each intervention session, the patients will be monitored for unwanted symptoms and adverse events and recorded in the patients study chart; 3) Symptoms experienced and adverse events will be discussed with individual patients weekly; 4) Adverse events will be a steady agenda at the weekly and monthly study group meetings; and 5) All adverse events will be reported by completing the hospitals unintended/accidental event form and will follow the hospitals procedure for reporting such events.

### Ethical considerations

There are presently no rehabilitation programs available for patients with acute leukemia at the Departments of Hematology (HH, RH), however upon approval from the physician, patients may be referred to a municipality rehabilitation program. Patients in both study arms are not inhibited from exercising during the study period, as long as it is in accordance with the departments’ safety guidelines for daily physical activity and social contact. Moreover, patients allocated to both the control and intervention groups will receive usual and optimal care during the study period.

#### ***Potential risks***

During the course of the trial, patients will receive two chemotherapy cycles and consequently experience two neutropenic periods, each lasting approx. 7–14 days and during this time patients are especially prone to experiencing unpleasant symptoms i.e. mucositis, fatigue, and complications i.e. bleeding and infections. Further, during the trial period, and as a requirement of usual care, patients will have an indwelling central venous catheter (CVC) placed in order to facilitate chemotherapy, transfusions and drug delivery. CVC’s have benefits (minimize extravasation risk and avoid discomfort), but are associated with certain risks (infection, thrombosis). Patients will therefore, be screened and observed (BP, P, T, platelets, hemoglobin, sign of infection or bleeding) prior to the physical tests and before and during each exercise session (see Pre-screening and safety precautions). We will integrate an adverse events procedure that includes observation, documentation, patient and study team awareness, discussion and reporting (see Tracking and monitoring adverse events). In our previous pilot study, no adverse events or injuries were observed as a result of the exercise [8], however two patients experienced aching in the hip area after increasing their walking distance and most patients reported slight soreness in their muscles the day after training. No bruising was noted. There were, however, two incidents during baseline testing of two patients, one female during the 6MWD tripped and fell to the floor, and a male patient fell forward and onto the floor during the sit-to-stand test. Both patients were not injured, and able to carry out the tests at a later time. Safety measures were then instituted immediately in the pilot study and these safety measures (using arm rests during the sit-to-stand test for weakened patients, patient information regarding wearing appropriate walking shoes) will continue during the RCT.

#### ***Approvals and registrations***

Study approval is obtained for Herlev Hospital and Rigshospitalet by the Scientific Ethics Review Committee of the Capital Region of Denmark (J.no. H-4-2010-046) and the Danish Data Protection Agency (J.no. 30–0431). The study is registered at ClinicalTrials.gov Identifier: NCT01404520.

### Statistical considerations

#### ***Sample size***

This randomized controlled trial will include 70 acute leukemia patients over a recruitment period of 34–36 months. Sample size calculation is based on the primary endpoint; the 6 min walk distance (6MWD) and the results from our pilot study (n = 20), where n = 17 completed the study (15% lost to followup). The pilot study baseline for 6MWD was 450 m and the average change was 56.3 m effect (SD = 69.2). Assuming that there is no change in the control group, an inclusion of 70 patients (35 intervention, 35 control) will yield more than 90% power (risk of type 2 error set at 0.10) to detect a difference of this magnitude between groups using a significance level of 0.05 (risk of type 1 error set at 0.05). Should 20% be lost to followup (n = 56), the power will still be larger than 80%.

### Analytic plan

#### ***Quantitative data***

Data will be entered into the OpenClinica database [64] and statistical analysis will be carried out using Statistical Analysis Systems (SAS) version 9.2. Procedures for data entry and audit program have been developed to ensure accurate data entry [65]. *Baseline comparisons* of demographic and clinical outcomes will be performed using independent samples t-tests, and chi-squared tests will be applied for categorical variables. The *primary endpoint* will be reported as an independent samples t-test comparing change scores in the two randomization groups. The *secondary endpoints* (physical and strength tests and PRO questionnaires) will be reported as means and 95% confidence intervals and medians inter quartile range (IQR) for continuous variable, while categorical data will be reported as proportions and compared across randomization groups using chi-squared tests. The intent-to-treat principle will be applied and the significance level is set at 0.05. *Additional analyses* of 6 and 12 month followup data (PRO questionnaires) and of weekly symptom measurements and physical activity data will utilize linear mixed models to quantify trajectories. The trials statistician ([name]) will prepare results without knowledge of assignment to randomization coding.

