### Randomization and group allocation

After baseline testing, patients will be randomized to one of two trial arms (intervention or control) using the computerized Clinical Trial Management System (CITMAS/HITMAS) [27] and stratified for age (<45 and >45 years), gender, and treatment facility (RH and HH). This is to ensure that the randomized groups are similar at baseline. A block design with allocation weight of 1:1 will be used to generate treatment allocation. Randomized patients will remain in the same group for the entire duration of the intervention.

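### The primary 6MWD analysis is a valid but unadjusted change-score t-test; a linear model with baseline 6MWD and the stratification factors would usually be more precise at no cost in data

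*Protocol article*

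**What the plan says.** Under Analytic plan, Quantitative data, the primary endpoint "will be reported as an independent samples t-test comparing change scores in the two randomization groups". No covariate, stratification term or adjusted sensitivity analysis is named for it. Linear mixed models appear in the same section, but only for the 6- and 12-month questionnaires and for the weekly symptom and activity data.

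Under Randomization and group allocation, the order of events is clear: "After baseline testing, patients will be randomized to one of two trial arms (intervention or control"). Allocation is "stratified for age (<45 and >45 years), gender, and treatment facility (RH and HH"), and the stated reason is "This is to ensure that the randomized groups are similar at baseline". On the method: "A block design with allocation weight of 1:1 will be used to generate treatment allocation". So baseline 6MWD and all three stratification factors are known for every patient before allocation.

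Under Sample size: "The pilot study baseline for 6MWD was 450 m and the average change was 56.3 m effect (SD = 69.2"). The calculation continues "Assuming that there is no change in the control group". It claims more than 90% power with 70 patients, and more than 80% if 20% are lost (56 patients).

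**The concern.** A t-test on change scores is a regression in which the coefficient of baseline is set to 1 rather than estimated. Where the true slope is below 1, the subtraction corrects too much, and part of any chance baseline difference stays in the estimate with its sign reversed. ANCOVA estimates the slope, removes that part and normally has a smaller residual variance.

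The second issue is the stratified allocation. Balancing the arms on prognostic factors reduces the true variability of the between-arm difference. A t-test that omits those factors does not credit this, so its standard error is too large and its type I error falls below the nominal 5%.

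With 28 to 35 patients per arm and a recruitment period of 34 to 36 months, precision available from data already collected is worth having. What is at stake is the width of the confidence interval and some power, not the validity of the conclusion.

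**Working it through.** **Inputs from the article (Sample size).** Difference 56.3 m; SD of change 69.2 m; 35 per arm, or 28 per arm after 20% loss; significance level 0.05, taken here as two-sided.

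**Inputs not in the article.** The baseline/follow-up correlation r, the baseline and follow-up variances, and how prognostic the strata are. These are assumed and varied.

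**1. The plan's own power.** Noncentral t with 2n − 2 degrees of freedom and noncentrality 56.3 / (69.2 × √(2/n)):
- n = 35: 56.3 / 16.54 = 3.40, power 91.8% (stated: more than 90%).
- n = 28: 56.3 / 18.49 = 3.04, power 84.8% (stated: more than 80%).

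Both statements reproduce.

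**2. Variance under ANCOVA, equal variances.** The change-score variance is 2σ²(1 − r) and the ANCOVA residual variance is σ²(1 − r²). Their ratio is (1 + r)/2, so the ANCOVA SD is 69.2 × √((1 + r)/2). Power uses 2n − 6 degrees of freedom (four covariates) and counts no gain from the strata.

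| r | Variance ratio | SD (m) | Power, 35/arm | Power, 28/arm |
|---|---|---|---|---|
| t-test | 1 | 69.2 | 91.8% | 84.8% |
| 0.5 | 0.75 | 59.9 | 97.2% | 93.1% |
| 0.6 | 0.80 | 61.9 | 96.3% | 91.6% |
| 0.7 | 0.85 | 63.8 | 95.3% | 89.9% |
| 0.8 | 0.90 | 65.6 | 94.2% | 88.2% |
| 0.9 | 0.95 | 67.4 | 93.0% | 86.5% |

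At 35 per arm the 95% CI half-width falls from 33.0 m to 28.6, 30.5 and 32.2 m at r = 0.5, 0.7 and 0.9.

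**3. Unequal variances.** Let k be the follow-up SD divided by the baseline SD. The slope is r × k and the variance ratio is k²(1 − r²) / (1 + k² − 2rk).
- r = 0.8, k = 1.25: 0.5625 / 0.5625 = 1. The slope is exactly 1 and ANCOVA saves nothing.
- r = 0.7, k = 1.1: 0.6171 / 0.67 = 0.92. The saving is about 8%, against 15% with equal variances.

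**4. Chance baseline imbalance, equal variances.** Given a realised baseline difference D, the change-score estimate shifts by −(1 − r)D. The implied baseline SD is 69.2 / √(2(1 − r)), and one standard error of the between-arm baseline difference is that SD × √(2/35).
- r = 0.5: SD 69.2 m, standard error 16.5 m, shift 8.3 m.
- r = 0.7: SD 89.3 m, standard error 21.4 m, shift 6.4 m.
- r = 0.9: SD 154.7 m, standard error 37.0 m, shift 3.7 m.

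Against 56.3 m these shifts are 15%, 11% and 7% (8.3/56.3, 6.4/56.3, 3.7/56.3).

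**5. Effect of the strata (simulation).** 4,000 trials per scenario, 70 patients, stratified permuted blocks, r = 0.5, 0.7 and 0.9. Assumed: block size 4 and factor prevalences of 30%, 50% and 65%.
- Strata explain 20% of residual variance (assumed): type I error of the t-test is about 3.0% to 3.7%, while the adjusted model stays near 5%. Power is about 93% to 94% for the t-test and 97% to 99% adjusted.
- Strata explain nothing: both methods hold about 5%. At r = 0.9 the simulated powers are then practically equal (91.6% and 91.7%), so the closed-form gain at that end of the table is at best marginal.

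**The case against.** The strongest defence is that nothing in the trial's inference is wrong. Over repeated randomisations the change-score t-test is unbiased. With prognostic strata it errs on the conservative side. The sample size was built on the SD of change, so design and analysis agree, and the power claims are met. The size of any gain also rests on quantities the article does not give. All of this stands, and it limits the point to efficiency.

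A reader might infer several stronger things that the document does not support:
- **That the analysis ignores baseline 6MWD.** It subtracts it; what it does not do is estimate the slope.
- **That chance imbalance enters the estimate in full.** Only the fraction 1 − r does so under equal variances, and only conditionally on the imbalance that occurs.
- **That a change score over-corrects whenever r is below 1.** That needs the slope r × k to be below 1; step 3 gives a case where it equals 1.
- **That continuous secondary endpoints have no treatment comparison.** The article says only that they "will be reported as means and 95% confidence intervals and medians inter quartile range (IQR) for continuous variable", but it plans mixed models for the follow-up questionnaires and weekly data. The between-arm model for the rest is detail that an article commonly leaves to the full plan.
- **That the age strata are defective because age 45 falls in neither.** This is probably a notation slip in a computerised scheme, and it has no bearing on the choice of test.

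One defence does not hold: that the matter belongs to an unseen analysis plan. The article names the primary test, so a plan that made an adjusted model primary would depart from it.

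**Conclusion.** The point holds as an improvement in efficiency, not as an error. The primary test leaves out covariates that are all recorded before allocation, three of which were important enough to stratify on. Assuming equal variances and r between 0.5 and 0.9, the variance saving is 25% to 5%, and power at 28 per arm rises from 84.8% to between 93.1% and 86.5%. The gain can be close to zero if r is high or if follow-up variance exceeds baseline variance. Any gain from the strata comes on top and depends on how prognostic they are. Confidence is high on what the article specifies and on the direction in general, and limited on the size, because r and the variances are not documented. The trial is not underpowered for the test it plans.

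**What to change.** Make the primary analysis a linear model of 12-week 6MWD on arm, baseline 6MWD, age stratum, gender and hospital. Name the 12-week visit explicitly, since 6MWD is also measured at 6 weeks. Report the adjusted between-arm difference with its 95% CI and p-value. Keep the change-score t-test as a sensitivity analysis, which preserves the link to the sample-size calculation. Code the age factor exactly as it was coded at randomisation.

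The cost is a change of wording in the analysis section and four residual degrees of freedom. No new data, visits or patients are needed. It should be fixed before the allocation is unblinded, so that adjustment cannot look like a response to an observed imbalance.

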#### ***Secondary endpoints***

*Aerobic capacity.* A single stage 6 min submaximal exercise test; the Aastrand-Rhyming cycle ergometer test is used to predict VO_2_ max values [48]. The test is based on the linear relationship between VO_2_ and heart rate. The patients pulse will be continually monitored using a wireless heart rate transmitter. Resistance (Watt) is increased to elicit a steady-state heart rate between 125 and 170 beats/min at a speed between 60 and 65 r.p.m. If after 6 min the HR is above 125 beats/min and stable, not fluctuating more than 5 beats/min, the test is terminated. VO_2_ max is determined using a nomogram with an age and body weight correction factor. VOs max is stated in ml/kg/min.

*Functional performance and muscle strength* comprises three endpoints: *(1)* Sit to stand test will be performed as a measure of strength and performance of the lower extremity muscles. The 30 second sit to stand was developed as an assessment tool to measure lower body strength [49]; (2) Biceps Arm Curl measures arm flexor strength, upper body strength and endurance [50]. The aim is to perform as many arm curls as possible in 30 seconds; and (3) Measurement of weekly steps and distance with the step counter: Omron Walking Style Pro [44].

*Clinical outcomes* (exploratory endpoints) will include andropometric characteristics *(*body mass index (wt(kg)/ht(m^2^)), WHO performance status, hospitalization (days), increased temperature (>38°) (days), elevated C-reactive protein (days), infections and complications (type and days), neutropenia and thrombocytopenia (days), transfusions (platelets and RBC) (number), time to relapse and survival.

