*Patient reported outcomes (PRO)* in this study are standardized and validated questionnaires that measure physical, functional, emotional and social wellbeing, symptom prevalence, intensity including fatigue and interference in daily activities. The PRO’s will be administered and checked for completeness by the study investigator at baseline, 6 and 12 weeks, and 6 and 12 months; and coded according to the guidelines given in the questionnaires manuals: (1) The Functional Assessment of Cancer Therapy-Anemia scale (FACT-An) assesses cancer specific Health Related Quality of Life (HRQOL), the fatigue symptom subscale (An) of the FACT-An scale and the Trial Outcome Index (TOI) [51]. (2) The 36-Item Short Form Health Survey (SF-36) assesses general wellbeing using eight scales measuring different aspects of general health with two summary scales; physical and mental component scales [52]. (3) The European Organization for Research and Treatment of Cancer Quality of Life Questionnaire (C30 EORTC QLQ-C30) assesses Quality of Life (QOL) using a global health status scale, five functional scales (physical, role, emotional, cognitive and social functioning) and symptom scales (fatigue, nausea and vomiting, pain, dyspnea, insomnia, appetite loss, constipation, diarrhea) [53,54]. (4) The Hospital Anxiety and Depression Scale (HADS) assess psychological wellbeing and is designed to measure general anxiety and depression in patients with physical illness [55]. (5) The M.D. Anderson Symptom Inventory (MDASI) assesses the severity of 13 symptoms and their impact as evaluated by six interference items [56]. The MDASI will be additionally administered once a week prior to the last training session. (6) The Brief Fatigue Inventory (BFI) assesses fatigue levels and their impact as evaluated by interference items [57]. The BFI will also be administered once a week prior to the last training session.

*Physical activity, social network/relations, activation and ability, and employment (return to work)* will be assessed by the (7) Leisure time physical activity [58], (8) Physical activity level [59], (9) Multidimensional Scale of Perceived Social Support (MSPSS) [60], (10) Patient Activation Measure (PAM) [61], (11) Self Efficacy Scale (GSE) [62] and (12) Employment status and ability [63].

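### Chi-squared tests for all categorical secondary outcomes ignore category order, which costs power wherever such an outcome is ordered with three or more levels

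*Protocol article*

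**What the plan says.** Under Quantitative data in the protocol article, the secondary endpoints are given in brackets and split by type. For the continuous ones the text reads "physical and strength tests and PRO questionnaires) will be reported as means and 95% confidence intervals and medians inter quartile range (IQR) for continuous variable". For the rest it reads "while categorical data will be reported as proportions and compared across randomization groups using chi-squared tests". It does not separate ordered, unordered and binary outcomes, and no other section names a test that uses category order. The same section sends the 6- and 12-month questionnaire data, the weekly symptom scores and the physical activity data to linear mixed models.

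Possible ordered outcomes appear under Secondary endpoints. The numbered questionnaires include leisure-time activity, activity level and "12) Employment status and ability". The clinical outcomes, labelled exploratory, include "WHO performance status, hospitalization (days" and further items. No number of levels is given for any of them.

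Under Sample size, the article states that "an inclusion of 70 patients (35 intervention, 35 control) will yield more than 90% power" for the 6-minute walk distance and continues "Should 20% be lost to followup (n = 56), the power will still be larger than 80" per cent. No power is claimed for any categorical outcome.

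**The concern.** The Background states a directional hypothesis: less loss of capacity, fewer symptoms, better wellbeing. On an ordered scale, such an effect moves patients towards the better grades. Pearson's test on k levels asks whether the arms differ in any way at all, on k − 1 degrees of freedom, and gives the same result if the levels are shuffled. A rank or trend test puts one degree of freedom on the shift that the trial expects. With 28 to 35 patients per arm there is little power to spare, so a real improvement on a graded item could be missed because of the choice of test alone.

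**Working it through.** **Inputs from the article.** 35 per arm, or 28 per arm after 20% loss (70 × 0.8 = 56). Alpha is 0.05, taken as two-sided because the article does not say. For the walk test, the effect is 56.3 m and the SD 69.2 m.

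**Inputs assumed.** Two to five levels, evenly spread or skewed, with a common odds ratio (OR) of 2 to 4 between arms. The article gives none of these.

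**Step 1: the plan's own figures.** Power ≈ Φ(δ/SD × √(n/2) − 1.96), with δ/SD = 56.3/69.2 = 0.814.
- n = 35: 0.814 × √17.5 = 3.403; Φ(1.443) = 92.6% (91.8% by noncentral t).
- n = 28: 0.814 × √14 = 3.044; Φ(1.084) = 86.1% (84.8% by noncentral t).

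Both agree with the stated figures of more than 90% and more than 80%. They concern the walk test only.

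**Step 2: the cost of extra degrees of freedom, large-sample.** Take a shift that a 1-df test detects with 80% power. Its noncentrality is (1.960 + 0.842)² = 7.85. The same noncentrality on k − 1 df gives power of 70.9% for three levels (2 df), 64.5% for four (3 df) and 59.5% for five (4 df).

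**Step 3: simulation at the trial's size.** 20,000 trials per setting compared Pearson chi-squared with the tie-corrected Wilcoxon rank-sum test. The intervention arm is shifted by dividing each cumulative odds by the OR. For example, with four even levels the cumulative odds are 1/3, 1 and 3. Dividing by an OR of 3 gives 1/9, 1/3 and 1, so the levels become 10/15/25/50%.

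Power at OR 3, even levels:

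| Levels | n = 35: chi-squared | n = 35: rank | n = 28: chi-squared | n = 28: rank |
|---|---|---|---|---|
| 2 | 58.9% | 58.9% | 49.3% | 47.0% |
| 3 | 56.3% | 67.3% | 47.3% | 57.6% |
| 4 | 52.8% | 70.3% | 42.6% | 60.1% |
| 5 | 48.5% | 71.4% | 38.3% | 61.1% |

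Relative loss = 1 − (chi-squared power)/(rank power). For four levels this is 1 − 52.8/70.3 = 25% at 35 per arm and 1 − 42.6/60.1 = 29% at 28. Across OR 2 to 4, both sizes and both even and skewed spreads, the loss is:
- two levels: none (0 to −7%, where the small apparent gain for chi-squared comes from the coarse set of possible tables);
- three levels: 10-25%;
- four levels: 16-38%;
- five levels: 20-47%.

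The loss is largest at small effects. With four even levels and 35 per arm it is 36% at OR 2 and 16% at OR 4.

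**Step 4: sparse cells.** With no true difference and skewed spreads over three to five levels, about 76-99% of tables had more than a fifth of their expected counts below 5. The type I error of chi-squared nevertheless stayed between 0.039 and 0.053. Sparseness makes the test at most slightly conservative. The power loss comes from the degrees of freedom.

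**The case against.** The strongest reply is that the article shows no secondary outcome that is certainly ordered and certainly tested by chi-squared. Most of the named questionnaires yield scores that the continuous clause can cover. Physical activity data may fall under the mixed models. WHO performance status is exploratory and outside the bracket that defines the secondary endpoints. Employment status may be binary or nominal, where chi-squared is a standard choice. All of this stands, and it makes the point conditional.

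A reader might infer that the trial gives up a quarter to a third of its power on its categorical outcomes. The documents do not support that. A figure of that size needs about four ordered levels and an OR near 2.5 to 3, and the article gives neither. A reader might also blame sparse cells, but step 4 shows no harm from them. Nor would a significant result be left without a direction, because proportions by arm are to be reported.

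A rank test does not rescue weak settings either. With four levels assumed at 20/40/30/10%, OR 2.5 and 28 per arm, chi-squared reaches 29% and the rank test only 44%.

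Finally, it can be said that such details belong in an analysis plan that is not shown. This does not dispose of the point. The article does not leave the test open: it names one test for every categorical outcome.

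**Conclusion.** The point holds in a conditional form. Wherever a categorical secondary outcome is ordered with three or more levels, the stated test ignores the order. At 28 to 35 per arm it then loses roughly 10-25% (three levels), 16-38% (four) or 20-47% (five) of the power that a rank test would have. These ranges rest on assumed spreads and a common OR of 2 to 4, meaning a shift in one direction. There is no loss for binary outcomes and no order argument for nominal ones. Which outcomes are affected cannot be settled from the article. The type I error is sound, and the walk-test analysis and its power statement are untouched. This is a modest improvement to secondary analyses, worth making because it costs so little.

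**What to change.** Add one sentence to the analytic plan: ordered categorical outcomes with three or more levels are compared between arms by a Wilcoxon rank-sum test or a linear trend test, and chi-squared is kept for binary and unordered outcomes. List which outcomes fall in each class.

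Optionally, report a common odds ratio with 95% CI from a proportional-odds model. Keep its covariates few, because a model with baseline category and all three stratification factors may be unstable with 56 to 70 patients. A general switch to Fisher's exact test is not needed: it is conservative and would gain no power.

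No new data are required. The small downside is that rank and trend tests are less sensitive to differences that do not run in one direction, such as patients moving from the middle to both ends of a scale.

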### Study endpoints and assessments

Outcome measures will be assessed at three time points, baseline, six and twelve weeks with a 6 and 12 month follow up. Table 3 outlines the study assessment schedule. Demographic, performance status (WHO) and medical data will be collected by journal review and questionnaire. Assessments will be carried out between 9:00 am and 12:00 noon by the project outcome assessors at their respective hospitals. Patients will be instructed on proper technique for the tests, and will be advised to stop if they experience pain or extreme discomfort, nausea, or dizziness. During the test sessions, the patients will be continuously monitored with a digital heart rate monitor (Polar Model) and observed for adverse reactions/events (see Monitoring Adverse Events).

**Table 3 T3:** Study assessment schedule

**Data Assessment**	**Screening**	**Day -2**	**Day 0**	**Day 1**	**6 weeks**	**12 weeks**	**6 months**	**12 months**
		**Baseline-test**			**Mid-test**	**Post-test**	**Follow-up**	**Follow-up**
*Recruitment*								
Chart review	x							
Patient approached	x							
Informed consent	x							
*Outcome Assessments*								
6MWD		x			x	x		
Aastrand-Rhyming test		x			x	x		
Sit to stand test		x			x	x		
Biceps arm curl		x			x	x		
Patient-reported outcomes		x			x	x	x	x
Medical chart review		x				x	x	x
*Weekly assessments*								
Step counter		x			x	x		
MDASI		x			x	x	x	x
BFI		x			x	x	x	x
PA Level		x			x	x	x	x
Randomization			x					
Intervention initiation				x				
Qualitative Interview						x		

**6MWD**, 6 minute walk distance; **MDASI**, M.D. Anderson Symptom Inventory; **BFI**, Brief Fatigue Inventory; **PA Level**, Physical Activity Level.

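### The primary t-test on 6MWD change names no visit and, without imputation, analyses only patients with a follow-up walk beside an intention-to-treat claim; a 12-week mixed model would fit better

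*Protocol article*

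**What the plan says.** In the protocol article, the Primary endpoint section names 6MWD and gives no time point. The general section on endpoints sets the timing: "Outcome measures will be assessed at three time points, baseline, six and twelve weeks with a 6 and 12 month follow up". For the walk, Table 3 narrows this to baseline, 6 weeks (column headed *Mid-test*) and 12 weeks (*Post-test*).

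The Quantitative data section makes the primary analysis a single two-sample t-test of change scores between the arms, and adds: "The intent-to-treat principle will be applied and the significance level is set at 0.05". It does not say which change score is tested. Mixed models appear only under additional analyses: 6- and 12-month questionnaire data and "weekly symptom measurements and physical activity data will utilize linear mixed models to quantify trajectories". The walk is not among them.

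The Randomization section stratifies by age group, gender and hospital, and places randomisation after baseline testing. The Sample size section says of attrition: "Should 20% be lost to followup (n = 56), the power will still be larger than 80" per cent.

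**The concern.** Three features of the primary analysis sit badly together.

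- **Who is analysed.** A change score needs a baseline and a follow-up walk. Without imputation, a randomised patient with no walk at the tested visit drops out. The n = 56 in the sample-size section counts patients in that way, while the analysis section claims intention-to-treat.
- **What information is used.** Two post-baseline walks are scheduled, but a two-point t-test uses one. It does not adjust for baseline distance or for the factors used to stratify randomisation. The plan already uses mixed models for other repeated measures.
- **Which visit is tested.** The time point is part of the primary endpoint, and it is open.

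Loss may be informative. The article expects two neutropenic periods with risks of infection and bleeding, and follows relapse and survival as outcomes. One arm attends three supervised sessions a week and the other receives usual care, so loss could differ between arms. The primary comparison would then partly reflect who stayed in the study. An unnamed visit also leaves room to choose between two results once the data have been seen.

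**Working it through.** **1. The plan's own power.** Inputs from the Sample size section: difference 56.3 m, SD of change 69.2 m, "Assuming that there is no change in the control group", 35 per arm, alpha 0.05. Sidedness is not stated and is taken as two-sided.

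Normal approximation: power = Φ(δ / (σ√(2/n)) − 1.96).

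- n = 35 per arm: 69.2 × √(2/35) = 16.54; 56.3 / 16.54 = 3.40; Φ(1.44) = 92.6%. Noncentral t: 91.8%.
- 20% loss: 0.80 × 70 = 56, or 28 per arm. 69.2 × √(2/28) = 18.49; 56.3 / 18.49 = 3.04; Φ(1.08) = 86.1%. Noncentral t: 84.8%.

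Both stated bounds are met. The second is a complete-case figure: 70 − 56 = 14 randomised patients are not in it.

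**2. Which visit.** The texts side by side:

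- Primary endpoint: no visit.
- Quantitative data: one t-test, no visit.
- Table 3: walks at 6 and 12 weeks, headed *Mid-test* and *Post-test*.
- Background: the aim is the effect of a 12-week programme. This points to 12 weeks.
- Sample size, with Background and Discussion: the 56.3 m comes from a pilot with a 6-week programme, so the planning effect does not settle the matter.

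The likely reading is 12 weeks, but no sentence fixes it.

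**3. What an open visit could cost.** Suppose either visit at 0.05 could be called the primary result. The false-positive rate is 1 − P(|Z1| ≤ 1.96 and |Z2| ≤ 1.96), with Z1 and Z2 bivariate normal with correlation r. The documents give no r, so a range is shown:

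| assumed r | rate |
|---|---|
| 0 | 9.75% |
| 0.5 | 9.1% |
| 0.7 | 8.3% |
| 0.8 | 7.8% |
| 0.9 | 7.0% |

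With one visit named in advance, the rate is 5% and the powers in step 1 stand.

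**4. Precision.** Let the walk have equal variance σ² at both visits and correlation ρ between baseline and follow-up. The variance of a change score is 2σ²(1 − ρ). The baseline-adjusted residual variance is σ²(1 − ρ²). Their ratio, adjusted to change score, is (1 + ρ)/2, which is below 1 for any ρ below 1. The article gives no ρ, so the gain is not sized here.

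**5. Bias from unequal loss, illustration only.** Let completers exceed non-completers by D metres in mean change, with the same D in both arms. The complete-case mean then exceeds the arm's full mean by (loss share × D), so the bias in the difference is D × (loss in intervention − loss in control). With D = 60 m and a 10-point gap: 60 × 0.10 = 6 m, which is 6 / 56.3 = 11% of the planned effect. With D = 100 m and a 15-point gap: 15 m, or 27%. No value of D or of the gap is in the documents; the only loss figure from experience is the pilot's 3 of 20.

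**The case against.** The strongest reply is that intention-to-treat can mean analysing patients in the arm to which they were randomised, which a change-score t-test respects. Imputation can precede a t-test, and rules for missing walks are commonly left to an analysis plan that is not shown here. The n = 56 is a power check under assumed attrition and does not define an analysis set. All of this stands. The article therefore does not show that intention-to-treat is abandoned, only that the method it names does not by itself carry the claim through.

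A reader might infer that the 0.05 level fails. The text does not support that: it describes one t-test and nowhere plans a test at both visits or lets either decide. The rates in step 3 apply only if the visit were chosen after seeing results.

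A reader might also infer that keeping all 70 patients would pull power below 80%. That depends on the assumption. If the lost 20% gain no benefit on average but vary as much as the others, power is about 74% to 77%. If every lost patient in both arms is given exactly zero change, the difference is 0.80 × 56.3 = 45.0 m, the SD falls to 63.9 m and power is 82.8%. The article's own sentence is conditional on 56 patients and is correct.

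The preferred model has limits too. It assumes that walks are missing at random, and a version restricted to patients with a post-baseline walk still omits some randomised patients. It improves on the t-test without delivering full intention-to-treat on its own.

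**Conclusion.** The point holds in a limited form. The primary visit is not named, and the named test, without imputation, analyses only patients with a walk at that visit. It also leaves unused the second scheduled walk, the baseline covariate and the stratification factors. The sample-size arithmetic is sound: 91.8% at 70 and 84.8% at 56 (t-test, two-sided), both as complete-case figures.

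The error risk from the open visit is about 7.8% to 9.1% at assumed correlations of 0.8 to 0.5. It is a risk from a choice left open, not a property of the stated plan. The 6 m to 15 m of possible bias is illustrative, because its inputs are assumed. The case for change rests on better precision and better handling of dropout at almost no cost, not on an error in the stated alpha or power.

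**What to change.** - **Endpoint:** state that the primary contrast is the between-arm difference in 6MWD at 12 weeks, with 6 weeks secondary.
- **Analysis:** replace the t-test with a linear mixed model over the baseline, 6- and 12-week walks, with arm-by-visit terms, age group, gender and site. Either adjust for baseline, or treat baseline as a response with its mean constrained equal across arms. In the constrained form every randomised patient with any walk contributes. Since baseline testing precedes randomisation, that should be everyone randomised, although a patient with only a baseline walk adds little about the treatment difference.
- **Sensitivity:** add an analysis for walks missing because of relapse, death or clinical deterioration, where missing at random is least credible.
- **Power statement:** label the n = 56 figure as complete-case.

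The cost is wording and slightly more analysis work, plus reliance on missing at random in the main model. No new visits, data or patients are needed, and the SAS software already planned fits the model. The change should be made before unblinded results are seen.
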